#### Trainer fidelity coding system development

Following the finalization of a Trainer Manual and accompanying resources, we will develop a fidelity monitoring observational coding system designed to capture the core ingredients needed for training skills in SBIRT. The goal of this fidelity monitoring coding system is to ensure a process for capturing the quality and consistency of the delivery of SBIRT training skills by trainers to health professionals and lay workers.

The coding system will contain elements of both trainer adherence (i.e., the consistency with which they delivered SBIRT training components) and trainer competence (i.e., the skill with which they delivered SBIRT training components), consistent with recommendations by Carroll and colleagues [46]. In the adherence dimension, the system will focus on coding elements such as coverage of key SBIRT components and inclusion of specific training components including didactic information, role-plays, and experiential learning. Such items will be coded fully/partially/not at all to denote whether the component was covered. In the skills dimension, the system will focus on rating the extent to which the trainers demonstrated effective skills such as participant engagement, time management, and responsiveness to questions. Consistent with other well-established scales of provider competence [47, 48], items will be coded on a 1–5 scale with 1 indicating “absent” and 5 indicating “fully present.” A coding manual will be provided to support reliable coding by an independent member of the South Africa International TTC who has knowledge of the SBIRT curriculum but who was not involved in training delivery. A score of 3 or above on each item will indicate an acceptable level of skill in training delivery.

#### Development of protocol for ongoing provider consultation

In addition to developing a Trainer Manual and fidelity coding system, our task sharing model will include the development of curriculum for ongoing consultation sessions. Consistent with the growing recognition that didactic training is more effective when paired with ongoing consultation [49, 50], all health professionals and lay workers that receive SBIRT training will have the opportunity to join monthly videoconference consultation calls, led by SBIRT trainers and coordinated by the South Africa International TTC. Each consultation call will begin with a brief didactic lesson about SBIRT delivery (approximately 15 min), and then the remainder of the session will be dedicated to a case presentation (i.e., example of HIV patient that receives screening for risky alcohol use that merits some form of brief intervention) followed by interactive group discussion. The South Africa International TTC team will develop a set of 12 brief didactic lessons covering themes such as: integrating HIV risk assessment into SBIRT delivery; detecting inconsistent screening responses; building motivation via the brief intervention; and effective referral to treatment.

In harmony with a task sharing approach, SBIRT trainers who completed the train-the-trainer session will be responsible for leading the didactic portion and soliciting volunteers for the case presentations. The goal of the consultation calls is to form a virtual hub-and-spoke knowledge sharing network, with the SBIRT trainers as the “hub” and the health professionals and lay workers as the “spokes” delivering SBIRT nationwide [51]. Each provider attending SBIRT training will be welcome to participate in monthly consultation calls for up to one year. The goal of these multi-point videoconference calls is to enhance the sustainability of the SBIRT training by reinforcing SBIRT skills on a routine basis.

#### Material refinement based on stakeholder feedback

Once the train-the-trainer curricula components have all been drafted (including the Trainer Manual, fidelity coding system, and ongoing consultation call curricula), the materials will be reviewed by members of the South Africa International TTC National Advisory Board. The National Advisory Board is comprised of over 30 representatives from 20 different national agencies and organizations^1^ and convenes twice per year to provide expert guidance to the South Africa International TTC. We will share the draft Training Manual and solicit feedback on the following themes, designed to help us refine and finalize the manual for roll-out in the field: a) ease and clarity of use by trainers; b) whether the manual captures the context and culturally specific elements needed for use in South Africa; c) whether examples used in the manual and learning exercises such as role-plays allow context-specific nuances across different cultural and language groups to surface adequately; d) whether core components of SBIRT are adequately covered; and e) whether skills needed for effective delivery of training to providers by trainers have been covered in sufficient depth.

### Phase 2 procedures

Phase 2 will involve implementation and evaluation of the SBIRT train-the trainer model described above, in order to address Study Aims 2 and 3. We will examine implementation of SBIRT using trainer-, provider-, and patient encounter-level outcomes over a 3-year horizon. Data will be collected immediately prior to the training, immediately after training, and again at 3- and 6-month follow-up assessments.

#### Participants

Participants will include a total of 24–36 trainers and 900 providers embedded within three distinct organizations (8–12trainers and 300 providers per organization). We will partner with three organizations or departments responsible for provision of HIV services, each of which has broad reach in HIV endemic regions and has a productive relationship with the South Africa International TTC. To be eligible for this protocol, partners must provide healthcare services to individuals in key populations either diagnosed with HIV or at heightened risk of HIV-related consequences (e.g., sex workers, inmates in correctional facilities, adolescent girls and young women). Each partner organization will nominate staff to receive SBIRT instruction from the South Africa International TTC and to become certified SBIRT trainers. To be selected as an SBIRT trainer, individuals must meet the following criteria: (a) be currently registered with a regulatory body relevant to HIV care (e.g., registered counselor, nurse, medical doctor, psychologist, social worker); (b) have been with their current organization for at least 1 year; and (c) have experience providing training and/or supervision to direct front-line treatment providers. Following nomination by their organization, the South Africa International TTC team will conduct a brief screen to confirm eligibility.

At each organization, the 8–12 SBIRT trainers will in turn roll-out the curriculum to a minimum of 300 providers (average training size = 25–30 participants), thereby reaching approximately 900 providers in Years 2–4 (300 providers per organization * 3 organizations = 900 providers). Providers selected to receive the training will include the full range of treatment providers whom our partner organizations seek to train in effective alcohol screening and brief intervention. Based on our initial needs assessment, we expect our training attendees to be predominantly (approximately 70%) lay workers, with some representation of registered counselors, nurses, doctors, psychologists, and social workers. We also expect the demographics of the behavioral health workforce (both trainers and providers) to generally mirror the composition of the South African population, as reflected in the most recent census: Black African (80.2%), White (8.4%), Coloured—a South African census term for a multiracial ethnic group—(8.8%), Indian (2.5%), and Other/Unspecified (0.5%; [52]).

#### Train-the-trainer model delivery

##### International TTC led train-the-trainer sessions

The South Africa International TTC will deliver SBIRT train-the-trainer sessions to those individuals nominated to become SBIRT trainers. These TTC-led sessions will be 2-days in duration, with assessments collected both pre- and post-training. The focus of these sessions will be to provide instruction in how to train in SBIRT. Attendees will receive the Trainer Manual developed in Phase 1, which will have all of the resources needed to deliver training to providers with limited experience delivering alcohol interventions (e.g., health professionals and lay workers).

Train-the-trainer sessions will culminate in substantial time spent practicing training delivery, with attendees pairing up to “role play”: one individual will practice the role of SBIRT trainer and the other will practice the role of training attendee. These role plays will be observed by a South Africa International TTC trainer, who will use the fidelity coding system to provide immediate feedback. If any of the trainers do not meet the pre-defined benchmark (see Measures) in their role play, the South Africa International TTC trainer will offer feedback on areas in need of improvement. For those trainers who meet the benchmark, positive reinforcement will be provided.

All attendees must complete a post-training knowledge test and at least one role play that meets the benchmark prior to being deemed a certified SBIRT trainer (see Measures for description of scoring and benchmarks). A specific criterion score on the post-training knowledge test is not required to proceed; however, those attendees scoring below the target will receive detailed corrective feedback from a South Africa International TTC trainer to ensure that they understand the key concepts covered in the training. By contrast, attainment of the benchmark score on at least one role play will be required. Those attendees who are unable to meet this requirement by the culmination of the 2-day session will be scheduled for Zoom practice sessions with the South Africa International TTC team. If a trainer does not meet the benchmark after three consecutive attempts, the partner organization will be notified and will have the option of sending the trainer back for re-training or selecting an alternate trainer. Once the benchmark is met, the attendees will be deemed official International TTC-certified SBIRT trainers.

##### Training sessions led by new SBIRT trainers

The certified SBIRT trainers will be required to lead at least one training within 3-months of their completion of the International TTC instruction. Each training will be 20–30 attendees, each of whom will receive the Provider Resource Guide. These SBIRT training sessions will be 1-day in duration. Training sessions will follow the same curriculum as the SBIRT train-the-trainer sessions, but will be streamlined given the removal of the content on how to effectively lead a training session. As with the initial train-the-trainer curriculum, there will be a substantial emphasis on role plays, though in these training sessions the role plays will focus on SBIRT delivery. Attendees will again pair up with one attendee playing the role of provider and another attendee playing the role of patient, using standardized case vignettes included in the Provider Resource Guide. Those providers receiving SBIRT training will be followed for 6-months and will provide outcome data at four distinct timepoints: immediately prior to didactic training, immediately post-training, 3-months post-training, and 6-months post-training, as elaborated in the following sections.

##### Ongoing monitoring and consultation

Ongoing support will be offered for both the SBIRT trainers and the providers in the form of periodic live observation and ongoing consultation calls. For certified SBIRT trainers, the South Africa International TTC team will go out into the field and live observe all of the scheduled SBIRT training sessions. The trainers will be informed in advance that their sessions will be observed as part of the ongoing monitoring process. Using the same protocol as the role play sessions, the observer will live code the training sessions using the fidelity coding system. The observer will provide private feedback at the end of these training sessions on training delivery in terms of both adherence and skill.

For providers, the South Africa International TTC will hold hourly videoconference consultation calls the last week of each month every day of the work week (i.e., five calls per month). The agenda and curriculum for these calls was described in Phase 1. Because SBIRT training rollout will be staggered and calls will be optional, attendance is expected to be manageable. More frequent sessions will be offered if attendance consistently exceeds more than 25 training recipients per call. Both attendance and engagement in these calls will be tracked as indicators of engagement in the train-the-trainer curriculum.

##### Post-training data capture

To evaluate the impact of training, attendees of the SBIRT training will commence recording data on their delivery of the AUDIT during patient encounters immediately after training with continuous recording of data for 6 months. As elaborated in the Measures section, patient encounter data will be tracked via programmed tablets or scannable paper forms, which will depict the AUDIT items and scoring algorithm.

Tablets and high-speed scanners will be offered to the partner organizations as an incentive for study participation: incentives are offered at the organization-level, reflecting the organization-wide focus of the train-the-trainer strategy. Each tablet and scanner will come with a brief user guide with step-by-step images showing how to answer the AUDIT questions using the technology. Tablets will enable off-line data collection and automated scoring using a highly intuitive user interface and robust data capture system, based around a platform called Survey2Go, though eventual connection with internet will be needed to submit data to the research team.

Our research team has developed and tested pre-programmed tablets as assessment administration and data collection tools with health professionals and lay workers in prior studies in South Africa [53]; the system has been applied in a wide range of contexts in South Africa ranging from no- to low-bandwidth, intermittent electricity, and in community and clinical contexts in both urban and rural areas. When tablets are not available or pragmatic such as in remote areas where even periodic internet connection is unlikely, providers will administer the AUDIT on user-friendly, one-page scannable forms using paper and pencil. Scannable forms will be sent to the research team in weekly batches for cleaning and aggregation.

### Measures

Prior to the start of training activities, leaders at each partner organization will fill out an Organizational Background Form that will contain data about key contextual factors that might be relevant to implementation including provinces served, key populations served, patient census, number of providers employed, and specific HIV services provided.

Once training activities commence, data will be collected from trainers, providers, and from case report forms capturing patient encounter data. The timeline of measure administration for the trainer-, provider-, and patient encounter-level data is shown in Table 2. For both trainers and providers, additional data collection will include basic socio-demographics including years of experience in the field, years of employment at the organization, biological sex, gender, South African population group (e.g., the equivalent of race/ethnicity in the United States), and education.

**Table 2 Tab2:**
[figure not shown]
Schedule of enrollment, training sessions, and assessments

*ToT* train-the-trainer; *TTC* Technology Transfer Center

#### Trainer-level measures

##### Trainer knowledge

At both the start and the end of South Africa International TTC-led training sessions, the attendees (the “SBIRT trainers”) will complete an SBIRT Knowledge Measure. This 20-item scale is based on an SBIRT Knowledge Test previously used in an SBIRT training initiative funded by Knopf-Amelung and colleagues [54], and has been tailored for the South African context. The scale contains true/false and multiple-choice items that assess knowledge of screening (e.g., how AUDIT scores are matched to risk zones) and brief intervention (e.g., steps of a brief interview, examples of motivational interviewing skills). A proportion of the number of correct items is used. Absolute scores range from 0 to 20, with 20 denoting the highest level of knowledge: these scores will be changed to proportions ranging from 0 to 100%. Attendees scoring below 70% on the post-training knowledge assessment will receive performance feedback from a member of the South Africa ITTC team.

##### Trainer fidelity

As noted previously, at the end of the International TTC led sessions, the International TTC team will observe the attendees completing role plays of training delivery. In addition, SBIRT training sessions will be observed to monitor fidelity. The South Africa International TTC observer will live code the trainer’s adherence and skill using the SBIRT Training fidelity monitoring checklist described in the “Trainer Fidelity Coding System Development” section. To score adherence, a point will be given for each training element fully covered and a half point will be given for each element partially covered. To score competence, each skill item will be rated from 1 to 5. The fidelity targets for both role plays and live observation will be 70% adherence, and a score of 3 or above on each of the skills items (i.e., “adequate” competence).

#### Provider-level measures

##### Provider attitudes

At four timepoints (pre-training, post-training, 3-months post-training, and 6-months post-training), providers will answer 10 items that capture both positive and negative (reverse scored) attitudes towards SBIRT. Example items include “Clients will be angry if I ask these questions” and “My involvement with a client can make a difference regarding his/her alcohol use.” Items are scored on 5-point scales from “Strongly Disagree” to “Strongly Agree.” Possible scores range from 10 to 50, with 50 denoting the best possible attitudes towards SBIRT. Measures of provider attitudes are from the SBIRT Implementation Toolkit developed by the Emergency Nurses Association [55].

##### Provider confidence

At the same time intervals as the provider attitudes scale, providers will answer 7 items that capture providers’ confidence in their ability to deliver SBIRT. Each item begins “I am confident in my ability to.” Example stems include “ask patients about their alcohol use,” “refer patients with alcohol problems,” and “discuss/advise patients to change their drinking behavior.” Items are scored on 5-point scales from “Strongly Disagree” to “Strongly Agree.” Possible scores range from 7 to 35, with 35 denoting the highest level of confidence. This scale is also from the SBIRT Implementation Toolkit [55].

##### Provider acceptability, appropriateness, and feasibility

Three brief, 4-item measures of acceptability, appropriateness, and feasibility will be administered at the same time intervals as the aforementioned provider scales. This collection of measures was developed by Weiner and colleagues [56] to facilitate pragmatic assessment of leading indicators of implementation success: the measures can be used separately or together and are designed to allow customization to a specific evidence-based intervention strategy. Acceptability will be measured via the Acceptability of Intervention Measure, which will contain the items “SBIRT is appealing to me” and “SBIRT meets my approval.” Appropriateness will be measured via the Intervention Appropriateness Measure, which will have items including “SBIRT seems applicable” and “SBIRT seems like a good match.” Feasibility will be measured via the Feasibility of Intervention Measure, which will have items “SBIRT seems implementable” and “SBIRT seems doable.”

#### Patient encounter-level measures

To evaluate how SBIRT training impacts provider-patient encounters, we will measure data from all patient encounters in the participating units of organizations in real-time using brief session report forms. These forms will be collected via programmed tablets and/or scannable forms administered by providers to patients. Patient encounter-level data will include the patient’s gender, race, HIV status, and whether the patient is currently receiving HIV treatment.

Additional fields will include documentation of the AUDIT screening results. The first two fields will be used to indicate (1) whether or not the patient is screened for alcohol use (yes/no) and (2) scores for each of the 10 items on the AUDIT. When completed via tablet, the sum of AUDIT items contained in Question 2 will auto-calculate. When completed via paper, providers will be given a basic scoring template to calculate and interpret the score. A user-friendly table will be provided that summarizes the patient’s risk level and recommended intervention in accordance with the risk algorithm(modeled after Table 1), while the tablet will directly indicate which level of care is recommended. This will result in field (3) recommended action based on AUDIT (which will either be automated on the tablet or clearly noted on the paper forms based on score), and then the provider can enter field (4) final action taken (no action taken, positive feedback / encouragement about drinking given, brief intervention provided, or brief intervention provided with referral to specialty care). Data collected using these fields will be used to assess a patient encounter-level measure of reach, calculated as the proportion of total patient encounters over the specified recall time period during which the patient received screening, brief intervention, and referral to treatment.

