**Fig. 1 Fig1:**
[figure not shown]
Conceptual model of the proposed implementation research

#### Specific aim 1

To finalize an SBIRT train-the-trainer model—consisting of an SBIRT Training Manual, Provider Resource Guide, case vignettes, fidelity monitoring coding system, and a protocol for provision of ongoing consultation—to promote SBIRT scalability to health professionals and non-specialist health workers.

#### Specific aim 2

To evaluate the effectiveness of the SBIRT train-the-trainer model on key implementation outcomes measured at the trainer- (i.e., knowledge and fidelity), provider- (i.e., confidence, attitudes, and acceptability), and patient encounter- (i.e., proportion of sessions in which patients are screened and receive a brief intervention) levels.

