#### Screening tool selection

The South Africa International TTC train-the-trainer curriculum will center around the Alcohol Use Disorders Identification Test (AUDIT), a 10-item questionnaire that was developed using data from a World Health Organization multi-national collaborative study, as the primary tool [40]. The AUDIT will be used as a focal screening tool because it is the only publicly available questionnaire that has been developed specifically for international use, has been translated into over 20 languages, and has demonstrated strong psychometric properties in South African treatment settings [41]. Scores for each item range from 0 to 4 with 4 denoting the highest level of risk: total scores range from 0 to 40. AUDIT scores will be used as part of a risk algorithm to tailor alcohol use intervention services to each individual’s risk profile. The SBIRT training curriculum will use the risk categories shown in Table 1, which align with recommendations of the South African Medical Research Council and the World Health Organization [42]. Instruction in this risk algorithm will comprise a major portion of the SBIRT training curriculum.

**Table 1 Tab1:** AUDIT-based risk algorithm and intervention recommendation

Zone	Score Range	Recommendation
1: Low risk	0–7 (no or infrequent hazardous drinking)	Positive feedback paired with simple information about alcohol and its effects on HIV
2: Medium-risk	8–15 (some hazardous drinking)	Brief intervention (e.g., brief risk reduction conversation based on Motivational Interviewing)
3: High-risk	16–19 (high-risk drinking causing harm)	Brief intervention paired with active case management
4: Very high risk	20–40 (probable alcohol use disorder)	Brief intervention paired with referral to more intensive treatment for an alcohol use disorder to reduce risk of re-infection, treatment non-adherence, disease progression, and serious alcohol-related consequences

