### Power analysis and sample size

We used data from our preliminary pilot work to formulate a realistic range of necessary assumptions for sample size and power considerations for primary outcomes (Table 3). Using our most conservative assumptions that rates of referral to treatment will only increase by 5% (at the lower end of rates reported in our preliminary study) and that the repeated measure correlation is only 0.3, we would need a complete sample of 488 to have sufficient power achieve power of 0.80 with a two-tailed alpha of 0.05. We expect an attrition rate of 20% over time (our prior studies in South Africa have attained retention rates of 85–100%): if we were to conservatively assume an attrition rate twice as high as expected (40%), we would need a sample of 683 to have adequate power. The proposed sample size of 900 is therefore extremely well powered to detect change in rates of screening, brief intervention, and referral to treatment over the course of the study. We propose 900 because it will increase our power to detect significant moderators: power will vary based upon the specific hypothesis and will be calculated using PowerUp! Software [65], but should be adequate to detect moderator effects at the provider- and provider encounter-level data. In addition, our proposed sample is reflective of the South Africa International TTC’s intention to roll out SBIRT nationally and train large cadres of health professionals and lay workers.

**Table 3 Tab3:** Power analysis and sample size (power = .80, alpha = .05)

	Repeated measure correlation	Pre-training rate	Post-training rate	△	Sample Size	
Screening	0.3	25%	40%	15%	107	
		25%	50%	25%	41	
		25%	60%	35%	22	
	0.5	25%	40%	15%	77	
		25%	50%	25%	30	
		25%	60%	35%	16	
Brief Intervention	0.3	20%	40%	20%	58	
		20%	50%	30%	28	
		20%	60%	40%	16	
	0.5	20%	40%	20%	43	
		20%	50%	30%	21	
		20%	60%	40%	13	
Referral to Treatment	0.3	10%	15%	5%	488	
		10%	20%	10%	142	
		10%	25%	15%	71	
	0.5	10%	15%	5%	353	
		10%	20%	10%	104	
		10%	25%	15%	53	

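### The final-action field on the encounter form has no code for the Zone 3 recommendation or for a referral without brief intervention, so Zone 3 delivery cannot be verified and the referral rate is open to coding error

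*Protocol article*

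**What the plan says.** Table 1 (Screening tool selection) sets four recommendations by AUDIT score:

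- Zone 1 (0–7): feedback with simple information.
- Zone 2 (8–15): brief intervention.
- Zone 3 (16–19): "Brief intervention paired with active case management".
- Zone 4 (20–40): "Brief intervention paired with referral to more intensive treatment for an alcohol use disorder".

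Under Patient encounter-level measures, field (3) holds the recommended action. The tablet generates it, or the paper form shows it, from an algorithm modelled on Table 1. In field (4) the provider then enters the final action taken, chosen from four options: no action, positive feedback, "brief intervention provided, or brief intervention provided with referral to specialty care".

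Reach is built from these fields as the proportion of encounters in which "the patient received screening, brief intervention, and referral to treatment". Specific aim 2 names the encounter-level outcome more narrowly, as the "proportion of sessions in which patients are screened and receive a brief intervention".

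The Power analysis section takes as its most conservative case that "rates of referral to treatment will only increase by 5" percentage points (10% to 15% in Table 3), which needs 488 complete cases. Under Post-training data capture, form recording starts after training. Under Analysis plan, the pre-training values come from baseline reports of the past 90 days.

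**The concern.** The form can recommend an action that it cannot record. A provider who follows Table 1 for a patient scoring 16–19 finds no field (4) entry that describes what was done. A provider who refers a patient without giving a brief intervention has no accurate entry either.

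Two things are at stake. The first is information. The article says that teaching the risk algorithm makes up a major portion of the curriculum, yet delivery of one of its four steps cannot be measured. The second is possible bias in the referral rate, one of the rates powered in Table 3. A provider who did more than a brief intervention has only one code that says so, and it says referral. About 70% of providers are expected to be lay workers, and the provider training lasts one day, so uniform handling of an unlisted action should not be assumed.

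**Working it through.** **1. Recommendations against codes**

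| Zone | Table 1 recommendation | Field (4) code that matches it in full |
|---|---|---|
| 1 | Feedback and information | Positive feedback |
| 2 | Brief intervention (BI) | BI |
| 3 | BI + active case management | None |
| 4 | BI + referral | BI with referral |

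Three of the four zones have a matching code. Zone 3 has none. Referral without BI also has no code, but Table 1 never recommends it.

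**2. Effect of the Zone 3 gap on the stated outcomes**

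- Coded as BI: BI is counted, correctly. Referral is not counted, also correctly. The bias is zero in both rates, and the case management goes unrecorded.
- Coded as BI with referral: BI is still counted correctly, but a referral is counted that did not occur.

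The BI rate is therefore the same under either code. For referral, observed rate = true rate + q, where q is the share of all encounters in which case management is coded as referral. The documents give neither q nor the Zone 3 share, so the values of q below are assumptions:

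| q | True referral rate | Observed |
|---|---|---|
| 0% | 15% | 15% |
| 1% | 15% | 16% |
| 3% | 15% | 18% |
| 5% | 15% | 20% |

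Each 1% adds one point, which is one fifth of the planned 5-point change. The lower limit is zero and the upper limit is the Zone 3 share.

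**3. Reproducing the plan's referral sample size**

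Inputs from Table 3: p1 = 0.10, p2 = 0.15, correlation 0.3, power 0.80, two-sided alpha 0.05.

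N = (1.960 + 0.842)² × [p1q1 + p2q2 − 2(0.3)√(p1q1p2q2)] / (p2 − p1)², where here q1 = 1 − p1 and q2 = 1 − p2
= 7.849 × [0.09 + 0.1275 − 0.6√(0.09 × 0.1275)] / 0.0025
= 7.849 × 0.15323 / 0.0025 = 481.1, so 482.

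A McNemar form gives 487 and a logit form 490. The stated 488 is reproduced closely, and this point does not contest it.

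**4. Referral-only encounters**

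Let s be the share of true referrals made without BI (assumed, because the documents give none). If these referrals are not recorded, the observed rate is 0.15(1 − s). If they are coded as BI with referral, the BI rate rises by 0.15s. The baseline is held at 10%, which assumes that the 90-day reports do count such referrals. Power is Φ(d/√(V/N) − 1.960), with d = observed rate − 0.10 and V the bracket in step 3. N = 720 is 900 less the expected 20% attrition.

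| s | Observed if dropped | Power, N = 488 | Power, N = 720 | BI inflation if forced into BI with referral |
|---|---|---|---|---|
| 0 | 15.0% | 0.81 | 0.93 | 0 |
| 5% | 14.25% | 0.68 | 0.84 | 0.75 points |
| 10% | 13.5% | 0.53 | 0.69 | 1.5 points |
| 20% | 12.0% | 0.22 | 0.31 | 3.0 points |

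These powers use the plan's own simple paired calculation and only show sensitivity to s. They do not forecast the trial's power.

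**5. Which side of the contrast**

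Field (4) entries exist only after training. Error that comes from the code list therefore enters the post-training rates and has no counterpart at baseline to cancel it.

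**The case against.** The strongest reply is that Zone 3 care does have a truthful code. The plain BI code is accurate though incomplete, no stated outcome counts case management, and with that code both rates are unbiased. Inflating the referral rate requires a false entry, and Table 1 teaches case management and referral as different things. All of this stands. It limits the Zone 3 gap to lost detail unless some providers record case management as referral.

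Misuse would also be partly visible, because field (2) keeps the AUDIT item scores. An analyst can count referral codes at scores of 16–19 and bound their effect. This stands too, but such a code cannot be resolved afterwards into a real referral or relabelled case management.

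The article may condense the actual form, which could have an open option or separate items. That is possible and lowers the severity. Even so, the article states a closed list joined by *or*, and that list does not match its own Table 1.

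Two stronger readings are tempting. A reader might infer that correct care is generally miscoded and that the brief-intervention and referral rates are both distorted. The documents do not support this. Only Zone 3 has on-algorithm care without a full code, the Zone 3 gap cannot move the brief-intervention rate, and referral without brief intervention is off-algorithm under Table 1. A reader might also infer that the referral rate will be inflated by the whole Zone 3 share. That is the upper limit and needs every such encounter to be coded as referral. The documents give neither the share nor any sign that such coding would be universal. Nor does the referral scenario fix the planned sample: 900 exceeds the 683 given for 40% attrition and is justified by moderator power and national roll-out.

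**Conclusion.** Table 1 and field (4) do not match, and they must be reconciled. As described, the form cannot distinguish full from partial delivery of the Zone 3 recommendation, and recommended and final action cannot be compared in that zone. This much follows from the text without any assumption.

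Bias in the rates is conditional. From the Zone 3 gap it is zero for brief intervention. For referral it runs from zero to the unstated Zone 3 share, at one point per 1% of encounters so coded. From referral-only encounters it can affect either rate, in a direction set by the code the provider chooses and with a size that depends on a frequency the documents do not give. Any such error is confined to the post-training side. The severity is below must-fix, but the repair is cheap and collected data could not be fully corrected later.

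**What to change.** On both tablet and paper, replace the single final-action list with four yes/no items: positive feedback, brief intervention, active case management, and referral to specialty care. No item ticked means no action taken. Count referral only from the referral item and brief intervention only from its own item. Each Table 1 recommendation, and any combination actually delivered, can then be recorded and set against field (3). This changes what is recorded and leaves the recommendations in Table 1 as they are.

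The cost is a small change to the form and the tablet program, plus one or two more ticks per encounter. The Data Availability section says that recruitment has not started, so no collected data would need recoding. If the full form already has separate items, correcting the article's description is enough.
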